### Participants included in analysis

All participants with complete data will be used for this study.

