### Secondary Outcomes

1. Prevalence changes of specific ARG classes (beta-lactam, macrolide, tetracycline, aminoglycoside resistance genes) measured at baseline, 2-week post-intervention, and 2-week washout periods.

2. Persistence of resistome changes during the washout phase (measured at 2 weeks post-intervention cessation) compared to baseline and intervention periods.

3. Identification of specific ARG signatures that appear or disappear following consumption of each fermented beverage.

4. Safety outcomes including participant-reported gastrointestinal symptoms and adverse events throughout the study duration.

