**Research Design**

This is a human intervention study with three arms (1:1:1 allocation ratio) designed to assess superiority of two fermented beverage interventions (Kunun Zaki and Kunun Aya) compared to a control group (no intervention) in modulating the gut resistome. The research follows a quasi-experimental design with participants assigned to different groups by chance to receive either *Kunun Zaki, Kunun Aya*, or no intervention for a 2-week period, followed by a 2-week washout phase. Sample collection occurs at baseline (pre-intervention), at the end of the 2-week intervention period, and at the end of the 2-week washout period.

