### Statistical methods for primary and secondary outcomes

ARG prevalence will be calculated for each group at baseline, post-intervention, and washout phases. Statistical comparisons between groups and across time points will be performed to determine the effect of beverage consumption on antimicrobial resistance gene patterns in the gut microbiota.

Statistical comparisons of ARG prevalence between groups will be conducted using appropriate parametric or non-parametric tests depending on data distribution. Significant differences in resistome composition will be determined using permutational ANOVA (PERMANOVA) at 95% Confidence Interval and 0.05α. Comparison of means will be done using an unpaired t-test and Tukey's multiple-comparisons test where appropriate.

ARGs will be categorized by resistance mechanism and antibiotic class to identify which categories are most affected by the intervention. Changes in clinically relevant resistance genes will be given particular attention in the analysis and interpretation of results.

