### Handling of missing data

Missing data will be documented and reported. For the primary outcome, participants with missing post-intervention samples will be excluded from the per-protocol analysis but included in intention-to-treat analysis using last observation carried forward where appropriate.

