**Ethical Consideration**

This research intends to simulate as close to natural as possible the habitual consumption of the local drinks by the participants, however there remains the risk of possible contamination of prepared drinks during handling by local sellers posing a limited threat to the health of participants (limited because they are used to consuming it ab initio from such sources). Participants will be directed to report any symptom of food poisoning for treatment and discontinuation of research for that participant, as well as other necessary precautions. There is also the concern about handling fecal matter for which participants will be trained on aseptic handling of fecal material, and be provided appropriate materials for same such as sample containers with an attached scoop for easier sample collection, and gloves.

**Confidentiality of data -** The sample bottles would be coded as simple as possible and will not be traceable to any of the volunteers. Names of subjects or identifiers will not be used in any publication or reports from this research. Any personal information collected during the research will be considered and treated as confidential.

**Translation of protocol to the local language -** the protocol will be translated to the local language of the subjects (Hausa) for few persons who may not understand English.

**Beneficience to participants -** After the research, participants will be able to know the positive impact of their diet type on their gut microbiota and by implication food digestion and absorption. Participants will also gain knowledge about antimicrobial resistance genes present in their gut microbiota.

**Non maleficence to participants -** the research will be conformed to professional standard thereby providing no risk to participants.

**Voluntariness --** participation is entirely voluntary

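### The complete-data rule names no outcome; applied literally to adverse events, it could leave out participants discontinued for food-poisoning symptoms

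*Protocol*

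**What the plan says.** Five places in the protocol bear on this.

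- **Participants included in analysis** is a single sentence: "All participants with complete data will be used for this study". Complete data is not defined, and no outcome is named.
- **Handling of missing data** follows directly. It begins "Missing data will be documented and reported" and then makes one relaxation: "For the primary outcome, participants with missing post-intervention samples will be excluded from the per-protocol analysis but included in intention-to-treat analysis", with the last observation carried forward where suitable.
- **Secondary Outcomes**, item 4, lists "Safety outcomes including participant-reported gastrointestinal symptoms and adverse events throughout the study duration".
- **Ethical Consideration** acknowledges that "there remains the risk of possible contamination of prepared drinks during handling by local sellers", and continues: "Participants will be directed to report any symptom of food poisoning for treatment and discontinuation of research for that participant".
- **Research Design** sets three stool collections: one at baseline, then "at the end of the 2-week intervention period, and at the end of the 2-week washout period".

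**The concern.** A complete-data rule is a choice one can debate for a laboratory outcome. It suits safety badly, because an adverse event is often the reason why later data are missing. Here the link is written into the protocol: the symptom itself triggers discontinuation. If the general rule governs safety too, being counted in the safety result can depend on not having had the harm.

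The harm in question is one that the protocol itself foresees. The drinks may be contaminated in handling, so a loss of cases would fall mainly on the two beverage arms. Controls come under the same reporting and discontinuation instruction and could lose cases as well. The trial enrols from age 3 and has 12 participants per arm, so losing one or two cases could turn a visible signal into none.

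**Working it through.** **Step 1: which rule governs safety?** The general rule covers the study as a whole. The one stated relaxation opens with the primary outcome, and its method (carrying a stool result forward) has no meaning for adverse events. Safety is a secondary outcome. For safety, therefore, the general rule is the only inclusion rule in this document.

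**Step 2: when would a food-poisoning case fail the rule?** Two conditions are needed, and the protocol neither states nor excludes either:

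1. stool sampling stops at discontinuation (the text speaks of discontinuing the research for that participant, which leans this way);
2. complete data means all three stools.

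If both hold, a participant discontinued during the beverage weeks lacks two of the three stools, and one discontinued during washout lacks the last. Both fall outside the set.

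**Step 3: is there a figure to reproduce?** No. The protocol gives no event rate, dropout rate or power calculation. Only the sample size can be checked: 3 arms × 12 = 36, as stated. Everything below uses assumed values.

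**Step 4: illustration in one beverage arm of 12.** Assume that k participants are discontinued for food poisoning, that all fail the rule, and that nobody else drops out. Counting all assigned gives k/12; counting complete data gives 0/(12 − k).

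| k (assumed) | All assigned | Complete data only |
|---|---|---|
| 1 | 1/12 = 8.3% | 0/11 = 0% |
| 2 | 2/12 = 16.7% | 0/10 = 0% |
| 3 | 3/12 = 25.0% | 0/9 = 0% |

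The zeros follow from the assumption that every case is lost. They show what the literal reading would do, not how likely it is.

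**Step 5: partial loss across the 24 beverage participants.** Let p be the true risk per participant and q the share of cases lost, with cases independent (a contaminated batch would cluster them). The chance that no case at all is counted is (1 − p(1 − q))^24.

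| p (assumed) | q = 0 | q = 0.5 | q = 1 |
|---|---|---|---|
| 5% | 0.95^24 = 29.2% | 0.975^24 = 54.5% | 100% |
| 10% | 0.90^24 = 8.0% | 0.95^24 = 29.2% | 100% |
| 20% | 0.80^24 = 0.5% | 0.90^24 = 8.0% | 100% |

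The column q = 0 is the outcome if safety is read separately from the stool data or if sampling continues: no loss at all. The column q = 1 is true by definition.

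As counts, 2/24 = 8.3% (exact 95% CI 1.0% to 27.0%) would become 1/23 = 4.3% (0.1% to 21.9%) if one case were lost, and 0/22 = 0% (0% to 15.4%) if both were. The intervals overlap widely.

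**The case against.** The best case on the other side is that the protocol contains no wrong statement about safety. The rule does not mention safety. It says that participants with complete data will be used, not that only they will be, and not that other participants' events are discarded. The section before it is headed "Statistical methods for primary and secondary outcomes" but describes only resistance-gene analyses, and the section after it speaks of missing samples, so the context points to stool data. Safety is self-reported: someone who reports food poisoning has supplied the safety datum, and read outcome by outcome nothing is lost. Missing data are to be documented, which would probably make a discontinued participant visible. A safety population is also ordinary content for a statistical analysis plan; the protocol mentions one, and it is not at hand.

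Most of this stands. It rules out the stronger reading that a reader might infer, namely that the protocol plans to drop these events or that harm will be under-reported. No text says so. Nor is the rule the only analysis set in the document, because per-protocol and intention-to-treat sets are named for the primary outcome.

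Two things remain. First, the point is about a rule that the protocol does state, in unrestricted terms, and not about a detail left for later. Second, documenting that a participant's data are missing does not place that participant's event in the safety results.

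**Conclusion.** The point holds as a risk created by wording. The inclusion rule has no limit of outcome, its relaxation reaches only the primary outcome, and the harm to be counted is itself a reason for leaving the study. Followed to the letter for adverse events, with sampling ending at discontinuation and completeness meaning three stools, the rule would remove the cases that the safety outcome should count.

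The size is unknown and cannot be derived from the protocol. It ranges from nothing, if safety is read on its own data, to 1, 2 or 3 cases in an arm of 12 being reported as 0, under assumed counts and complete loss. The calculations show a possible bias, not an established one. The matter is worth correcting because the correction is small and specific, not because a distorted result has been shown.

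**What to change.** In the section on participants included in analysis, restrict the complete-data rule to the resistance-gene (resistome) analyses. Then add a sentence such as: *Adverse events and gastrointestinal symptoms are reported by arm for all assigned participants, whether or not their stool samples are complete, including events that led to discontinuation.*

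The cost is one or two sentences and slightly more tabulation. No new data, staff or procedures are needed, because participants are already told to report these symptoms. If this was the intention all along, the edit changes nothing in practice. If a statistical analysis plan defines a safety population, the protocol sentence should be brought into line with it.

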### Handling of missing data

Missing data will be documented and reported. For the primary outcome, participants with missing post-intervention samples will be excluded from the per-protocol analysis but included in intention-to-treat analysis using last observation carried forward where appropriate.

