## Primary and Secondary Outcomes

### Primary Outcome

The primary outcome is the change in gut resistome composition, measured as the difference in total antimicrobial resistance gene (ARG) abundance and diversity between baseline and post-intervention timepoints (2 weeks). This will be quantified using ARG detection by PCR, with results analyzed at the conclusion of the 2-week intervention period. The primary endpoint compares ARG profiles between the intervention groups (Kunun Zaki and Kunun Aya) and the control group using permutational ANOVA (PERMANOVA) with alpha set at 0.05.

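### Carrying the last observation forward can only copy baseline into week 2, so it imputes zero change in the primary outcome, and the stated analysis population does not fit this rule

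*Protocol*

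**What the plan says.** - **Sampling (Protocol, Research Design):** "Sample collection occurs at baseline (pre-intervention), at the end of the 2-week intervention period, and at the end of the 2-week washout period". Baseline is the only sample before week 2.
- **Primary outcome (Protocol, Primary Outcome):** the change in resistance genes from baseline to the two-week sample, with each beverage arm compared with control "using permutational ANOVA (PERMANOVA) with alpha set at 0.05".
- **Missing data (Protocol, Handling of missing data):** for this outcome, "participants with missing post-intervention samples will be excluded from the per-protocol analysis", but they are "included in intention-to-treat analysis using last observation carried forward where appropriate". The section does not say when carrying forward is appropriate.
- **Who is analysed (Protocol, Participants included in analysis):** "All participants with complete data will be used for this study".
- **A route to missing samples (Protocol, Ethical Consideration):** "Participants will be directed to report any symptom of food poisoning for treatment and discontinuation of research for that participant". The contamination risk described there comes from the prepared drinks, which controls do not receive.

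**The concern.** Carrying an observation forward presupposes an earlier on-treatment value. This schedule has none before week 2. A participant who drank the beverage but gave no week-2 sample would enter the intention-to-treat analysis with a pre-intervention profile labelled as post-intervention, and the analysis would treat it as observed.

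In arms of 12, one such participant is 8% of the arm (1/12). The distortion falls on the primary comparison, and its direction depends on whether the control arm also changes over the two weeks. Separately, the section that defines who is analysed describes people with complete data, while the next section admits people who lack the very sample that the primary outcome needs.

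**Working it through.** **Inputs from the Protocol.** 12 per group and 36 in all (Sample Size); 3 × 12 = 36 agrees. The number was set on feasibility. No effect size, SD, power or dropout rate is given, so the plan has no further figure to reproduce. There are three sampling times (Research Design), and the primary outcome is change from baseline to week 2 (Primary Outcome).

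**Step 1: the imputed value.** Imputed change = carried value − baseline = baseline − baseline = 0. For the 12 gene targets listed under Antimicrobial Resistance Gene Detection, all 12 results are duplicated, so the person shows no gene gained and none lost.

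**Step 2: one arm's mean.** If k of 12 are missing and would have changed like the rest (true mean change m), the arm's mean becomes m × (12−k)/12. The factor is 11/12 = 0.92, 10/12 = 0.83 and 9/12 = 0.75 for k = 1, 2 and 3.

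**Step 3: the contrast between arms.** With T for beverage and C for control, the expected difference is

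m_T(12−k_T)/12 − m_C(12−k_C)/12.

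- Only the beverage arm changes (assumed m_T = −1.2 SD, m_C = 0): −1.10, −1.00 and −0.90 SD for k_T = 1, 2 and 3. The effect is diluted.
- Both arms change equally (assumed −1 SD each), 3 missing in the beverage arm only: −0.75 − (−1) = +0.25 SD. A difference appears where none exists.
- Neither arm changes: 0. No bias.

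**Step 4: illustration by simulation.** 100,000 runs, 12 per arm, SD of change 1, samples missing completely at random. An unpaired t-test on change scores at two-sided 0.05 stands in for PERMANOVA. All effect sizes and missing counts are assumptions.

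| Scenario | Missing in beverage arm | Carried forward | Observed data only |
|---|---|---|---|
| True difference −1.2 SD: power | 0 | 80% | 80% |
| | 1 | 73% | 78% |
| | 2 | 65% | 76% |
| | 3 | 56% | 73% |
| No difference, both arms −1 SD: type I error | 3 | 8.5% | about 5% |
| | 4 | about 12% | about 5% |

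**Step 5: the standard error.** With 3 zeros among 12 and SD 1, the expected sample variance is (8.25 + 2.25m²)/11 = 0.75 + 0.2045m². The squared standard error is this divided by 12, against 1/9 for the nine observed participants. The two are equal when 0.75 + 0.2045m² = 12/9 = 1.333, so m² = 2.85 and m is about 1.7 SD. Below that the zeros make the arm look more precise than nine observations justify; above it they make it look less precise.

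**Step 6: the two population statements side by side.** A set of participants with complete data and an intention-to-treat set with carried-forward values are the same only if no sample is missing. The complete-data statement matches the per-protocol set in Handling of missing data and not the intention-to-treat set beside it.

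**The case against.** The strongest reply has four parts.

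1. *The two sections need not contradict each other.* Participants included in analysis does not say that nobody else is analysed. It could be read as describing the per-protocol set, and the choice of primary set may sit in an SAP that is not shown. This stands in part: a reader might infer two flatly incompatible rules, and the wording does not go that far. But the section's heading makes it the definition of who is analysed, and it does not cover the intention-to-treat set named next. The two need aligning. That neither set is labelled primary is not counted as a fault here.

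2. *Carrying forward is cautious, because it pulls toward no effect.* A reader might infer that the bias always runs toward zero. It does so only when the control arm is stable; Step 3 gives a case where it creates a difference. It is also tempting to say that it always understates uncertainty, but Step 5 shows that this depends on the size of the change.

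3. *Missingness related to arm is not established.* This stands. Ethical Consideration calls the risk limited because participants already drink these products. Loss concentrated in the beverage arms is plausible, since discontinuation follows food-poisoning symptoms and controls receive no drink, but the Protocol gives no rate. If no week-2 sample is missing, the rule does nothing to the primary outcome.

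4. *The (12−k)/12 figure describes a mean, and the primary test is PERMANOVA on profiles.* This also stands. The figures show size and direction; they do not predict the PERMANOVA result.

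The qualifier about appropriateness does not rescue the rule, because no other earlier value exists to carry. Nor does the fact that the summary's sampling description also uses the term post-intervention for the washout sample: the rule is stated for the primary outcome, which is tied to two weeks.

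**Conclusion.** The point holds. It follows from the schedule alone that carrying forward imputes zero change whenever a week-2 sample is missing. This is a rule that the Protocol states, not a detail left to the SAP.

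The size is a factor of 0.92, 0.83 or 0.75 on an arm's mean change for 1, 2 or 3 of 12 missing, provided that missing participants would have changed like the others. If those lost have disturbed guts, that assumption may fail and the error could be larger or smaller. The contrast between arms may be diluted or falsely created, depending on change in the control arm and on where samples are lost. The actual impact cannot be known from the Protocol.

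The definition of who is analysed must also be reconciled with the intention-to-treat set. The documents do not support saying that the bias has one fixed direction or that dropout will differ by arm.

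**What to change.** 1. **Handling of missing data:** delete the carry-forward rule. Define one primary set: all assigned participants with the baseline and week-2 samples needed for the contrast, analysed in the arm assigned and whatever their adherence. Keep PERMANOVA, on observed samples only.
2. **Participants included in analysis:** revise to name the same set. Asking for the two samples needed, and not all three, keeps more people. If each sample were missing independently with an assumed probability of 5%, 10% or 15%, about 32, 29 or 26 of 36 would have both (36 × (1−p)²), against about 31, 26 or 22 with all three (36 × (1−p)³).
3. **Sensitivity analysis:** add one under stated missingness assumptions. For per-person gene counts or the presence of single genes, a repeated-measures model on all available samples can serve. It is not a drop-in replacement for PERMANOVA on the 12-gene profile, and it relies on data being missing at random.
4. **Handling of missing data and Ethical Consideration:** clarify whether the stool samples already planned are still collected from participants who stop the beverage. The clinical decision to stop is left as it is.

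The cost is Protocol wording, a little more analysis, slightly fewer participants in the primary analysis and, if sampling continues, a few non-invasive samples that were already planned.

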**Ethical Consideration**

This research intends to simulate as close to natural as possible the habitual consumption of the local drinks by the participants, however there remains the risk of possible contamination of prepared drinks during handling by local sellers posing a limited threat to the health of participants (limited because they are used to consuming it ab initio from such sources). Participants will be directed to report any symptom of food poisoning for treatment and discontinuation of research for that participant, as well as other necessary precautions. There is also the concern about handling fecal matter for which participants will be trained on aseptic handling of fecal material, and be provided appropriate materials for same such as sample containers with an attached scoop for easier sample collection, and gloves.

**Confidentiality of data -** The sample bottles would be coded as simple as possible and will not be traceable to any of the volunteers. Names of subjects or identifiers will not be used in any publication or reports from this research. Any personal information collected during the research will be considered and treated as confidential.

**Translation of protocol to the local language -** the protocol will be translated to the local language of the subjects (Hausa) for few persons who may not understand English.

**Beneficience to participants -** After the research, participants will be able to know the positive impact of their diet type on their gut microbiota and by implication food digestion and absorption. Participants will also gain knowledge about antimicrobial resistance genes present in their gut microbiota.

**Non maleficence to participants -** the research will be conformed to professional standard thereby providing no risk to participants.

**Voluntariness --** participation is entirely voluntary

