### Rationale for the Study

Kunu contains beneficial bacteria as well as blended cereal (fibre) which makes it suitable to serve both as a probiotic through gut microbiota modulation, and prebiotic by stimulating the growth of other bacteria. The fermentation process in Kunun production involves lactic acid bacteria which may competitively exclude potential pathogenic bacteria and their associated resistance genes. Understanding how traditional fermented beverages affect the gut resistome is important for public health, particularly in regions where antimicrobial resistance is a growing concern and where these beverages are regularly consumed.

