### Exclusion criteria

Engaging in any of these during 2 weeks prior to the first sample collection; antibiotic use, intentional intake of probiotic or prebiotic products, presence of gastrointestinal disorders such as diarrhea, inflammatory bowel disease, or irritable bowel syndrome, pregnancy or breastfeeding, alcoholism and drug addiction. For the entire 6 weeks this research will last for, participants will be required to report their daily food and drug intake using an individualised web app developed for this purpose.

Interventions and Comparator

**Intervention 1 - Kunun Zaki:** Participants will consume 500 mL of Kunun Zaki daily for 2 weeks. Kunun Zaki is a traditional Nigerian fermented beverage made from millet or sorghum, supplemented with ginger and cloves as spices.

**Intervention 2 - Kunun Aya:** Participants will consume 500 mL of Kunun Aya daily for 2 weeks. Kunun Aya is a traditional Nigerian fermented beverage made from tiger nuts, prepared through similar fermentation processes as Kunun Zaki.

**Control:** Participants in the control group will maintain their habitual diet without any intervention beverage for the 2-week period.

All participants will be instructed to maintain their usual dietary habits aside from the intervention beverage. Interventions will be delivered by study personnel who will ensure participants receive fresh beverages daily. Adherence will be monitored through daily self-reported logs via the web-based food diary.

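### Self-sourced Kunu is unrestricted in washout and unnamed in the run-in exclusion, although participants are described as habitual drinkers, so persistence cannot be told apart from resumed drinking

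*Protocol*

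**What the plan says.** - **Background exposure.** Ethical Consideration says the study is meant to "simulate as close to natural as possible the habitual consumption of the local drinks by the participants" and rates the contamination risk from local sellers as "limited because they are used to consuming it ab initio from such sources". The Rationale refers to regions "where these beverages are regularly consumed". No amount or frequency is given.
- **Nature of the drink.** The Rationale says the composition of Kunu "makes it suitable to serve both as a probiotic through gut microbiota modulation, and prebiotic".
- **Run-in.** The Exclusion criteria list "intentional intake of probiotic or prebiotic products", limited by "Engaging in any of these during 2 weeks prior to the first sample collection". Neither Kunu nor fermented drinks in general are named. The Summary adds a two-week monitoring phase in which a daily recall checks compliance with these criteria.
- **All arms.** Under Interventions and Comparator: "All participants will be instructed to maintain their usual dietary habits aside from the intervention beverage". The Summary has the assigned beverage, 500 mL daily, added to the habitual diet.
- **Controls.** "Participants in the control group will maintain their habitual diet without any intervention beverage for the 2-week period".
- **Washout.** Two weeks, with a sample at the end. Secondary outcome 2 is persistence of resistome changes at that point, compared with baseline and with the intervention period. No restriction on intake is stated.
- **Diary.** Daily food and drug intake is reported for all 6 weeks. The diary records intake and sets no rule on it.

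**The concern.** A washout is informative only if exposure stops. Here the participants are said to drink the product anyway, are told to keep their usual habits, and meet no rule on the product once the intervention ends. A change still present at the washout sample could be a lasting effect or could reflect Kunu bought from a local seller the week before.

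The baseline has a related problem. Every change score starts there, yet the protocol does not say whether a habitual drinker should have stopped Kunu by then. If participants read the exclusion differently, the starting condition differs between people and, by chance with 12 per arm, between arms.

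**Working it through.** No figure in the protocol quantifies background intake, so there is nothing to reproduce beyond the layout: 3 arms × 12 = 36 participants, and 2 + 2 + 2 = 6 weeks, both as stated. The check is a comparison of the text by phase, followed by simple algebra.

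**Rules on self-sourced Kunu by phase**

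| Phase | Beverage arms | Control arm |
|---|---|---|
| Run-in (2 weeks) | Probiotic and prebiotic exclusion; Kunu not named; usual diet | Same |
| Intervention (2 weeks) | Assigned drink plus usual diet; other or extra Kunu not addressed | Habitual diet, without the intervention beverage |
| Washout (2 weeks) | No rule | No rule |

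**Run-in.** Two readings are possible.
1. Kunu counts as a probiotic or prebiotic, as the Rationale describes it. Habitual drinkers must then stop or are ineligible, which conflicts with keeping usual habits.
2. Kunu does not count, because a customary drink need not be an intentional probiotic product. Baseline is then taken under exposure.

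The daily recall does not settle this, since it checks compliance with the same unclear criterion.

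**Washout.** Set the full effect of current drinking to 1 and no exposure to 0. Let f be the share drinking at baseline, g the share drinking in washout at an intake similar to the assigned one, and r the part of the effect that truly persists after stopping. None of these is in the protocol; each can lie anywhere from 0 to 1.
- Mean level at baseline: f. At week 2 in a beverage arm: 1. At washout: g + (1 − g)r = r + g(1 − r).
- Fall from week 2 to washout: 1 − [r + g(1 − r)] = (1 − r)(1 − g).
- Change from baseline to washout: r + g(1 − r) − f.

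The fall is symmetric in r and g, so the data cannot separate them. Half the effect persisting with nobody resuming (r = 0.5, g = 0) gives a fall of 0.5. No persistence with half the arm resuming (r = 0, g = 0.5) also gives 0.5.

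Against baseline, the direction depends on the run-in reading:
- Clean baseline (f = 0), no true persistence (r = 0): the apparent persistence equals g, that is 0, 0.25, 0.5 or 1 for g = 0, 0.25, 0.5 or 1.
- Exposed baseline with the same habit resumed (f = g): the change is r + g(1 − r) − g = r(1 − g), so true persistence is understated. With r = 0.5 and g = 0.5 it is 0.25.

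**Primary contrast with control.** On the same scale, if controls abstain during the intervention weeks and any earlier effect has reversed by week 2, their change is 0 − f = −f. The beverage arm changes by 1 − f. The difference is (1 − f) − (−f) = 1, so nothing is lost. It shrinks to 1 − f only if controls go on drinking as before: (1 − f) − (f − f) = 1 − f.

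**The case against.** The strongest reply is that the control arm is protected where it matters most. The control instruction rules out the intervention beverage in exactly the window that feeds the primary comparison. A reader might infer from the habitual-drinker description that control, baseline and washout are all contaminated and that the primary effect is diluted by a calculable amount. The document does not support that. It keeps controls without the beverage for those 2 weeks, the run-in exclusion may already cover Kunu, and no habitual intake is given from which to compute a loss. This part of the reply stands.

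What remains for controls is an ambiguity. For a habitual drinker, keeping the habitual diet and going without the beverage cannot both be followed, and going without may mean not drunk or merely not supplied. If controls do stop, habitual drinkers are compared as continuing or increasing against withdrawing, which is a different question from adding the drink to an unchanged diet.

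It is also fair to say that extra intake on top of a natural diet is a legitimate question and matches the stated aim of imitating habitual use. That could justify leaving background intake alone during the intervention weeks, but it cannot justify a washout without cessation. Finally, the diary should make such intake visible. That helps description, but seeing the exposure afterwards does not restore a clean washout.

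**Conclusion.** The point holds for washout and, as an unresolved contradiction, for baseline. As written, secondary outcome 2 cannot distinguish persistence from resumed drinking, and the error can run in either direction depending on how run-in is read. It could affect all three arms, since none has a washout rule. In the intervention weeks, the beverage arms have no rule on the other Kunu or on extra Kunu, and the control wording needs clarifying.

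No size can be attached, because habitual intake is not documented. The algebra is a simple linear illustration that assumes a similar dose from self-bought drink. Actual contamination is not demonstrated, nor is dilution of the primary contrast with control. This should be corrected before enrolment, because these are rules of conduct that no later analysis can replace.

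**What to change.** Reconcile the Summary, the Rationale, the Exclusion criteria with Interventions and Comparator, and Ethical Consideration through one explicit statement in the eligibility and intervention section:
- For each arm, and separately for run-in, intervention and washout, say whether self-sourced Kunun zaki and Kunun aya may be drunk. Write the rule so that washout is free of both drinks and the baseline condition is the same in all arms.
- Say whether Kunu falls under the probiotic and prebiotic exclusion, and whether the control instruction means not drunk or not supplied.
- Record habitual Kunu frequency at entry.
- Verify with the 6-week diary, and report off-protocol Kunu by arm and phase.
- Treat any analysis that leaves out participants with off-protocol Kunu as supportive only. Drinking after assignment may be related to arm and outcome, and with 12 per arm such exclusions risk selection bias.

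The cost is protocol wording and one question at entry; the diary is already planned. The real downside is a somewhat less natural diet for habitual drinkers, which pulls against the stated aim of imitating ordinary consumption and should be acknowledged.
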